#### Cognitive Load

We will assess the cognitive load experienced by participants using the questionnaire developed by Klepsch et al [29]. This instrument allows for a separate evaluation of intrinsic load (the inherent difficulty of the content), extraneous load (the load imposed by the way information is presented), and germane load (the effort invested in meaningful learning). We will use the version with a total of 8 statements rated on a 7-point Likert response (“not at all true” to “completely true”). Examples of items include “The content was very complex” (intrinsic load), “The way the information was presented was confusing” (extraneous load), and “I invested a lot of effort into understanding the material” (germane load). All 3 scales showed good internal consistencies (Cronbach α >0.80 in similar studies), allowing the use of mean scores across all items of a scale as the final score.

#### Perceived Learning

We will ask participants to self-assess their perceived learning from the activity. This will be done with 3 custom questions adapted from prior studies on perceived learning [30]. Responses will indicate agreement on a 7-point Likert response from “strongly disagree” to “strongly agree.” The 3 questions are “Overall, I was satisfied with my learning experience,” “This type of learning met my needs as a learner,” and “I could learn well with the material presented.”

### Procedure

Each participant will attend a single session, either individually or in small groups, depending on laboratory capacity. Even when in groups, each participant will complete the study independently at their own workstation (with individual screens and headphones).

#### Orientation (5 Min)

Participants are welcomed and seated at a computer or tablet station. Written informed consent is obtained if not already collected during recruitment. Participants then complete a short intake form to gather demographic information (age, gender, and specialty area), confirm their participation in the Facharztprüfung preparation course, and verify their English proficiency and lack of prior exposure to the study materials. They are also screened for any sensory impairments that might interfere with reading or listening tasks.

Participants are randomly assigned to one of the counterbalanced order conditions (ie, whether they first read the narrative article or listen to the technical podcast, or vice versa). The researcher then provides access to the appropriate learning material.

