**Methods:**

We designed a 2×2 mixed factorial study with 60 resident physicians preparing for the board certification in internal medicine or cardiology. All participants will engage with 2 peer-reviewed cardiology articles differing in complexity: a narrative case report on eosinophilic myocarditis and a technical research article on quantifying the vena contracta area using 3-dimensional echocardiography. Each participant will read 1 article and listen to an AI-generated podcast summary of the other, with the order and assignment counterbalanced to control for order effects. The podcasts are created using Google NotebookLM’s experimental *audio overview* feature. Participants will complete a multiple-choice knowledge test for each article. The primary outcomes are comprehension scores for each modality. The secondary outcomes include intrinsic motivation, perceived learning gains, and cognitive load for each condition. Data will be analyzed using a mixed ANOVA to test the main effects of modality and article complexity, as well as their interaction.

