### Study Design and Setting

We will conduct a single-center, 2-factor mixed experimental study with a 2×2 design. The within-subjects factor is the learning modality (AI-generated podcast vs traditional reading), and the between-subjects factor is the presentation order (ie, which article-modality combination comes first). Each participant will engage with 2 cardiology articles—1 practical case report and 1 technical research paper—experiencing 1 via reading and the other via an AI-generated podcast. The assignment of modality to article and the sequence of presentation will be fully counterbalanced across participants to control for order effects and content bias.

The study will take place at LMU Munich. Each participant will attend a single study session, during which they will read 1 article and listen to the other in podcast form. After each learning task, participants will complete a multiple-choice knowledge test and questionnaires assessing motivation, cognitive load, and perceived learning.

All study sessions will be conducted in a controlled classroom environment at LMU Munich. A researcher will be present throughout the study to supervise the session and ensure adherence to the protocol. The physical setting will be quiet, with individual desks and study materials provided on desktop computers or tablets. Participants in the podcast condition will be provided with noise-canceling headphones to standardize audio delivery.

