#### AI-Generated Podcasts

Using Google NotebookLM (an AI platform currently in experimental release) [24,25], we generated an audio summary for each of the 2 articles. The process involves uploading the article text into NotebookLM and then using the “audio overview” feature. The output is an audio file featuring 2 synthetic voices (the *AI hosts*) discussing the article. According to NotebookLM’s design, the hosts begin by introducing the topic, then proceed to discuss key points, clarify terms, and make connections. This is similar to one host quizzing or interviewing the other about the article’s content. The tone is meant to be conversational, which can help maintain listener interest.

Google NotebookLM was chosen for this study because, at the time of design, it was the only publicly accessible platform capable of generating conversational, dialogue-style audio summaries directly from full-text academic articles with no need for additional scripting. Its *audio overview* feature automatically organizes content into a simulated exchange between 2 hosts. This format aligns with well-established educational strategies, such as elaborative interrogation and peer explanation, which can foster learner engagement and retention. While alternative AI tools can produce summaries, they typically provide plain-text outputs or monologue-style narrations and require substantial manual adaptation to achieve a similar conversational format. Using NotebookLM enabled us to create standardized, pedagogically relevant podcasts with minimal human editing, thereby reducing the risk of inadvertent bias in the intervention materials while maintaining ecological validity for real-world use cases.

Each resulting podcast is approximately 15 minutes in length. The audio files are in English, matching the article's language. We reviewed the transcripts of these AI-generated discussions to ensure they cover the main sections of the articles (eg, the case presentation and outcome in the narrative article, and all major subtopics in the technical article). We also checked for any factual inaccuracies or misrepresentations.

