#### Primary Analysis

To assess the effect of learning modality and article complexity on comprehension, we will conduct a 2×2 mixed ANOVA with the following factors:

Within-subjects factor: modality (AI-generated podcast vs traditional reading)Within-subjects factor: article complexity (narrative case report vs technical research article)

Each participant completes both a reading task and a podcast task, 1 with the narrative article and the other with the technical article. The assignment of modality to article is counterbalanced. We will test for the main effects of modality and complexity, and their interaction, on knowledge test scores (range 0-10 per article). Effect sizes will be reported using eta squared (η²). Assumptions of normality (Shapiro-Wilk test on residuals) and homogeneity of variance (Levene test) will be examined. If assumption violations are detected, we will consider using robust ANOVA procedures [31].

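### The randomisation step names only one modality–article pairing plus an ambiguous *vice versa*, so it does not clearly deliver the counterbalanced assignment that the interaction test needs

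*Protocol article*

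**What the plan says.** Orientation (5 Min) states that "Participants are randomly assigned to one of the counterbalanced order conditions" and explains these conditions, after *ie*, as "whether they first read the narrative article or listen to the technical podcast, or vice versa". The swapped pairing (narrative heard, technical read) is not spelled out there.

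Study Design and Setting describes a 2×2 design with modality as the within-subjects factor and adds that "the between-subjects factor is the presentation order (ie, which article-modality combination comes first". Sample Size Calculation likewise has order as its single between-subjects factor. The same design section also promises more: "The assignment of modality to article and the sequence of presentation will be fully counterbalanced across participants". The Abstract agrees ("with the order and assignment counterbalanced to control for order effects"), as does Primary Analysis ("The assignment of modality to article is counterbalanced").

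The section on the podcasts reports that "we generated an audio summary for each of the 2 articles". On the analysis, the plan is explicit: "We will test for the main effects of modality and complexity, and their interaction, on knowledge test scores".

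**The concern.** Counterbalancing both the pairing and the order takes two pairings × two orders, which is four sequences. The allocation text names the two tasks of one pairing and calls what is randomised an order condition. Read that way, every participant reads the narrative article and hears the technical one, and only the sequence varies.

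Under that reading, modality and complexity are one and the same contrast. The protocol expects lower scores on the technical article, so any difference between podcast and reading would carry the whole difficulty difference between the two tests. The interaction, which is the study's specific hypothesis, would have no data behind it. No analysis could repair this afterwards.

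**Working it through.** **Sample size.** N=44 does not settle how many groups were intended. The inputs f=0.25, α=0.05 and power 0.80 are stated; the correlation ρ between the two scores and the number of groups g are not. For m=2 measurements, λ = f²·N·m/(1−ρ).

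- Two groups (within effect or interaction), ρ=0.35 (assumed): λ = 0.0625 × 44 × 2 / 0.65 = 8.46 on 1 and 42 df. Power is 0.811 and the required N is 44.
- Four groups, within effect, ρ=0.35: the required N is again 44.
- Four groups, interaction on 3 df: 48 at ρ=0.5 and 40 at ρ=0.6.

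So 44 is compatible with two groups and, for the within effect, with four.

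**What each reading can estimate.** Code modality M (podcast +1, reading −1), article A (technical +1, narrative −1), their product MA, and period. Then check the rank of the design matrix with columns [1, M, A, MA], and again with period added.

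| Sequences used | Cells filled | corr(M, A) | Rank without period | Rank with period |
|---|---|---|---|---|
| One pairing, two orders | 2 of 4 | 1.0 | 2 of 4 | 3 of 5 |
| Two pairings, two orders | 4 of 4 | 0 | 4 of 4 | 5 of 5 |

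With one pairing, MA equals +1 in every row, so it cannot be told apart from the intercept. At N=60 the cells hold 60, 0, 0 and 60 observations. With four equal sequences there are 60/4 = 15 participants per sequence and 30 observations per cell.

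Two pairings with the article order held fixed would fill all four cells, but article would then be aliased with period (correlation 1.0; rank 4 of 5). Both pairings and both orders are therefore needed.

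**Why pairing itself must be randomised.** Let R and P stand for reading and podcast, and N and T for the narrative and technical articles. The interaction is

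(RT − PT) − (RN − PN) = (RT + PN) − (PT + RN).

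The right-hand side is the summed score of participants with the swapped pairing minus that of participants with the named pairing. It is a between-participant comparison, although Primary Analysis lists both factors as within-subjects. Randomisation protects it only if participants are randomised to a pairing. Randomising order alone does not do this.

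**Possible size of the bias, one-pairing reading only.** The podcast-minus-reading difference would equal the modality effect plus the technical-minus-narrative difference. The article gives no figure for the latter. If the technical test is 1 to 3 points of 10 harder (assumption), the contrast shifts against the podcast by that full amount. For comparison, f=0.25 for two equal groups is a difference of 2 × 0.25 = 0.5 SD, or 1 point if the SD is 2 (assumption).

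**The case against.** A reader might infer that the trial is confounded by design. The article does not support that.

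- The words before *or vice versa* already cover both orders of one pairing. The phrase adds something only if it means the swapped pairing, and then all four sequences are covered. The Debriefing section uses the phrase for a swap of modality.
- Counterbalanced assignment is stated in three places, and the randomisation sentence itself calls its conditions counterbalanced.
- A podcast was made for both articles. The narrative podcast has no use as a learning task under one pairing. Descriptive Statistics also plans summaries by modality and complexity.
- The between-subjects factor is glossed as the article–modality combination that comes first. Four combinations exist, and the first fixes the second, so the factor could have four levels.
- This is a condensed article. The allocation list is not shown, and nothing shows that it contains one pairing only.

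Most of this stands, and it makes two pairings the likelier intention. The four-level argument is weaker. Study Design and Setting calls modality by presentation order a 2×2 design, which gives order two levels. Descriptive Statistics also illustrates order group by whether reading or listening came first. Nor is this mere missing detail: the article does give an allocation rule, and that rule has two readings, one of which makes the primary analysis impossible.

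**Conclusion.** The point holds as an inconsistency in the description of the randomisation. The Orientation text and the 2×2 description in Study Design and Setting do not clearly deliver the counterbalanced assignment stated in the Abstract, Study Design and Setting, and Primary Analysis.

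The consequence depends on the reading. If only order is randomised, modality and article are fully aliased and the interaction cannot be estimated; this is algebra and needs no assumption. If the swapped pairing is included and randomised, modality and article are uncorrelated and every effect is estimable. The 1-to-3-point shift applies only to the first reading and rests on an assumed difference in test difficulty. Confounding is a risk of one reading and not the established design, but the primary question depends on which reading is carried out.

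**What to change.** In Orientation, replace the parenthesis with the four sequences:

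1. read narrative, then podcast technical;
2. podcast technical, then read narrative;
3. podcast narrative, then read technical;
4. read technical, then podcast narrative.

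State that participants are randomised equally across them, about 15 each at N=60. In Study Design and Setting and in Sample Size Calculation, state that pairing (which article is heard) as well as order is randomised between participants. Check that the allocation list contains all four sequences.

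The cost is wording and that check. The article reports that no one had been recruited at submission in August 2025, so the correction belongs before the first session.

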#### Learning Phase 1 (30 Min)

Participants begin with their first learning task: either reading 1 article or listening to the podcast version of the other. Each participant has up to 30 minutes for this phase, which accommodates the full podcast duration (approximately 12 min) or sufficient reading time (approximately 15 min) with sufficient buffer. Participants are instructed not to take notes or use external aids. The researcher monitors to ensure compliance (eg, that readers are not using mobile phones or writing and that listeners are not replaying segments excessively).

#### Knowledge Test 1 (5 Min)

Immediately after the first learning task, the materials are removed. Participants complete a multiple-choice quiz assessing their comprehension of the content they just engaged with.

#### Posttask Questionnaire 1 (5 Min)

Participants complete a brief questionnaire assessing intrinsic motivation, cognitive load, and perceived learning for the first learning task.

#### Break (Optional, Approximately 2 Min)

A short, optional break (2-3 min) may be offered to reduce carryover fatigue between tasks.

#### Learning Phase 2 (30 Min)

Participants proceed to their second learning task, which is in the opposite modality and with the alternate article. Again, materials are provided for up to 30 minutes, and participants are instructed not to take notes or access external resources. The researcher continues to monitor the session.

#### Knowledge Test 2 (5 Min)

As before, the article or podcast is removed, and participants complete a second multiple-choice quiz focused on the second learning task.

#### Posttask Questionnaire 2 (5 Min)

Participants complete the same set of questions (motivation, cognitive load, and perceived learning) for the second task.

#### Debriefing (5 Min)

After all tasks are complete, the researcher provides a brief debriefing. Participants are informed about the study’s purpose and hypotheses and may ask questions. If they are interested, they are offered access to the alternate format for each article (eg, if they read the case report, they may request the podcast version, and vice versa). Participants are politely asked not to discuss the study specifics with peers until the study has concluded to minimize bias for future participants.

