## Methods

All study materials (articles, audio files, and questionnaires) and deidentified data will be made available in an open science repository [20] upon study completion, in line with open science practices.

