#### Exclusion Criteria

We will exclude individuals who have prior extensive familiarity with the specific articles used in the study. During recruitment and again at the start of the experimental session, we will present the titles and journal references of the 2 articles. If a participant confirms that they have previously read, studied, or discussed either article in detail (eg, in a journal club or as part of examination preparation), they will be thanked and excluded from participation to avoid a knowledge bias.

Additionally, individuals with uncorrected hearing impairment or severe visual impairment that would prevent them from effectively listening to the audio podcast or reading the article will be excluded. Because each participant will engage in both a reading and a listening task, we require all participants to have unimpaired or corrected functional access to both modalities.

We will recruit participants from a structured board examination preparation course organized by LMU Munich. This course attracts physicians actively preparing for their specialty certification and therefore reflects a highly motivated and relevant target group. Participants will be informed about the study through announcements made during the course sessions and follow-up emails. The study will be presented as a research project on learning from medical articles using different formats, without disclosing specific hypotheses. Participation is entirely voluntary and will not affect their standing in the course or the certification process.

Before participation, each physician will receive a full briefing on the study’s goals, procedures, and data privacy protections. This study will generally be described as a comparison of different learning formats for medical content. Written informed consent will be obtained. We will emphasize that participation is voluntary, performance on the comprehension tests has no bearing on their training or certification, and all data will be anonymized and treated confidentially.

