#### Informed Consent

As noted, we obtain written informed consent from all participants. They are informed that the study is about learning from the medical literature and involves completing tests, but the full details of the interventions are somewhat masked until debriefing to preserve the blinding of the hypothesis. They are told that they can withdraw at any time without penalty.

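### Disclosing the hypotheses and offering the study materials at the end of each session puts hypothesis masking and the prior-exposure exclusion at risk for classmates not yet tested

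*Protocol article*

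**What the plan says.** Five places in the protocol article bear on this.

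- **Debriefing (5 Min).** "After all tasks are complete, the researcher provides a brief debriefing". Purpose and hypotheses are explained at that point, and "If they are interested, they are offered access to the alternate format for each article". The section ends with a safeguard: "Participants are politely asked not to discuss the study specifics with peers until the study has concluded to minimize bias for future participants".
- **Procedure.** "Each participant will attend a single session, either individually or in small groups, depending on laboratory capacity".
- **Exclusion Criteria** (which also holds the recruitment text). "We will recruit participants from a structured board examination preparation course organized by LMU Munich". The study is announced there without its specific hypotheses. People who already know either article in detail are excluded. They are asked at recruitment and again at session start, with titles and references shown both times.
- **Orientation (5 Min).** The intake form also confirms that the participant has had no earlier contact with the study materials. The opening of Methods counts the articles, audio files and questionnaires as study materials.
- **Informed Consent.** "the full details of the interventions are somewhat masked until debriefing to preserve the blinding of the hypothesis".

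The opening of Methods adds that materials and data "will be made available in an open science repository" once the study is complete.

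**The concern.** The debriefing is timed to the individual participant, whereas masking and the exposure exclusion have to last until the final participant has been tested. Between the first and the last session, a growing number of people in the same course know the hypotheses and have been offered the podcast or article they did not receive.

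Two things are at stake.

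1. **Expectation effects.** Participants know whether they are reading or listening. Motivation, cognitive load and perceived learning are self-ratings, so knowing what the investigators expect could colour the answers.
2. **Prior exposure.** A later participant who has already heard a podcast and is then assigned to read that article has received both modalities. If they say so, they are excluded on the day. If they do not, their score no longer reflects the assigned modality alone.

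The podcast matters more here than the articles. Both articles are published and their titles are shown at recruitment, so a curious recruit can find them anyway. The podcasts were made for the study.

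**Working it through.** The point rests on no figure in the plan, so the check is mainly a comparison of sections.

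**Can debriefed and untested participants overlap?** Debriefing is inside the single session (Debriefing). Sessions are individual or in small groups (Procedure), and 60 people are planned (Sample Size Calculation). They cannot all be tested at once, so some are debriefed before others are tested. The request in Debriefing itself refers to participants still to come.

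**Are they in contact?** They are recruited from one preparation course (Exclusion Criteria). How often it meets and how long recruitment lasts are not stated.

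**What can pass between them, and what stops it?**

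| What could leak | Barrier at the source | Check on the later participant |
|---|---|---|
| Hypotheses | Polite request not to discuss | None stated |
| Podcast | Same request, worded about discussion and not about passing on a recording | Intake self-report of exposure to study materials, which include audio files |
| Articles | Same request, but the articles are already published | Self-report at recruitment and at session start |

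The first row has no check at all. The other two depend on honest self-report.

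**Whose data can be affected?** Debriefing comes after both tests and both questionnaires, so it cannot affect the data of the person debriefed. Only later participants are exposed, and only if someone talks or shares.

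**What would honest reporting cost?** Inputs from Sample Size Calculation: about 44 required, 60 planned.

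- Reserve: 60 − 44 = 16, and 16 / 60 = 26.7%.
- The 44 depends on a correlation between the two scores that the article does not give. With noncentrality λ = f²·N·m / (1 − ρ), f = 0.25, m = 2 and two groups, ρ = 0.35 gives λ = 0.0625 × 44 × 2 / 0.65 = 8.46 at N = 44 and power 0.811, which agrees with the stated figure.
- At other correlations the requirement for the within-subjects effect is 66 (ρ = 0), 46 (ρ = 0.3) or 34 (ρ = 0.5). The reserve is then −6, 14 or 26.

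Exclusions for exposure would share this reserve with ordinary dropout and missing data, assuming those excluded at session start count among the 60.

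**Can the leakage itself be sized?** No. With groups of 6 (an assumption, as group size is not stated), (60 − 6) / 60 = 90% would be tested after the first debriefing. Tested one at a time, it would be 59 / 60 = 98%. These count opportunity. They do not say how many would learn or receive anything.

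**The case against.** A reader might infer that masking and the exposure exclusion are bound to fail. The documents do not support that, for these reasons.

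- **The risk was recognised.** The non-disclosure request is made for the sake of later participants. Whether a request is enough is a matter of degree. This stands.
- **The exposure check is wider than the exclusion text suggests.** Exclusion Criteria speaks of the articles, but the Orientation intake covers the study materials, and Methods counts audio files among them. It would be wrong to say that the session-start check misses the podcast. It can fail only through inaccurate self-report. This stands.
- **Masking is partial by design.** The article calls it "somewhat masked until debriefing to preserve the blinding of the hypothesis", and participants are told beforehand that learning formats are being compared. Nor is masking the only protection, since assignment is randomised and counterbalanced and sessions are supervised. This stands and lowers the stakes.
- **The hypotheses in Textbox 1 concern knowledge scores.** For motivation, cognitive load and perceived learning the article announces a comparison without a direction. Leaked hypotheses would carry no explicit expectation for those ratings, although someone told that reading should do better on the complex article could still carry that over. This largely stands.
- **Leaked content should not systematically favour one modality.** Modality is counterbalanced over articles, so prior exposure should fall on reading and listening alike. The likely result is noise or a ceiling effect. A claim of directional modality bias is not supported.
- **Access is on request, and its timing is not stated.** Nothing says that a transferable file is handed over or that test questions are released. This stands, but it is also a reason to fix the timing in the text.

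The repository statement is not a contradiction either. It governs public release, whereas the debriefing offer is to people who have finished. It does show that holding materials until study completion is already foreseen.

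**Conclusion.** The point holds as a preventable risk to later participants. The hypotheses are disclosed and the alternate formats offered while classmates may still be untested. The protections are a voluntary request and self-report, and nothing checks whether a later participant knows the hypotheses. The documents do not show that masking or the exclusion fails, and they give no basis for a direction of bias in the modality contrast.

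The extent of leakage cannot be computed, and the 90% and 98% figures should not be read as contamination rates. The conclusion assumes that sessions are spread over time, which follows from individual or small-group testing, and that course members have some contact with one another, which is likely but not stated. The weight is minor to moderate. It merits action because contamination cannot be repaired afterwards and prevention is cheap.

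**What to change.** 1. In Debriefing, limit the end of the session to thanking participants and repeating the confidentiality request. The request could usefully mention passing on materials as well as discussing the study.
2. Send the explanation of purpose and hypotheses, with access to the alternate formats, to all participants after the last session.
3. In Informed Consent, change the point up to which details are masked from the debriefing to the end of data collection, and tell participants at consent that a fuller explanation will follow.

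Randomisation, sample size and analysis stay as they are. Emails are already used in recruitment, and the article reports that no one had been recruited at submission. The costs are a delayed debriefing and a contact list that must be kept apart from the coded data. The published articles remain findable from the titles shown at recruitment, so the change mainly protects the podcasts and the hypotheses.
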